**Methods:**

This proposed digital nutrition education intervention study targets technologically limited older adults enrolled in the congregate meal program (CMP) using a stepped-wedge clustered randomized controlled trial. Key community partners, City of San Antonio Department of Health Services Senior Services Division and OATS, contributed to the study’s planning phase, research design, and implementation. The 20-week intervention included 5 weeks of in-person technology training, including internet access and technical support for 1 year and devices, followed by 15 weeks of a culturally tailored online nutrition education intervention. The study randomized 398 older adults from 12 congregate meal sites. Data collection took place at baseline, 3 months, 6 months, 9 months, 12 months, and 18 months. If successful, the impact of this program could be applied throughout the national OATS network and to similar CMPs to bridge the digital divide beyond the COVID-19 pandemic.

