## Methods

### Design

This study is a closed cohort stepped wedge design in which the timing of the intervention is randomized by cluster, with the sequential crossover of clusters from control to intervention until all clusters have received the intervention. With this design, each cluster contributes data when they are participating in the intervention and when they are not. Stepped wedge designs are useful for several reasons. First, they allow all participants to receive the intervention, and each intervention arm can serve as its control, which decreases the number of units needed. Second, the design is practical in a situation with limited resources where the intervention logistically cannot be carried out all at once. Third, the design allows researchers to examine any effects of time on the intervention’s effectiveness [36,37]. Baseline data on current dietary intake, food security, malnutrition, technology use and attitudes, physical activity, social isolation, loneliness, and demographics were collected from all participants at Time 0. Each of the 12 centers was randomly assigned to one of 2 cohorts. Participants in Cohort 1 received the intervention first. Once Cohort 1 participants finished the intervention, a crossover occurred as Cohort 2 participants began the intervention. At the 12-month time point, the second cohort completed the intervention. Data will be collected for both groups each time point from T0 to T3 (Figure 1).

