### Power Calculations and Estimation of Sample Size

Our sample size calculation was conducted based on examining the effect sizes of similar studies in the current literature [68]. Effect sizes for fruit and vegetable intake ranged from 0.41 to 0.8 [9,28]. Using the smaller effect sizes and considering the stepped wedge design as a clustered randomized trial, with an Interrelation Class Coefficient of 0.016 [37] estimated from the literature (thereby reducing our effective sample size), a total of 210 participants (105 per group) is required to reach 80% power. With an expected N*=*410 participants in the analytic sample (effective N=374), we will be able to detect an effect size of 0.30 with 80% power and 97.7% power to detect an effect of 0.41 [69]. To detect a difference with an effect size of 0.3 or greater with 80% power at an alpha level of 0.05, 352 participants are required in the analytic sample. Power was calculated using the stepped wedge command in STATA/SE (12.1; StataCorp LLC). The details are described in Hemming and Girling [36].

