To assess the long-term impacts of the program at T3, Level 1 (time) will model the change in the outcome variables throughout the study (T0, T1, T2, and T3) within each participant. Specifically, each participant’s random intercept (eg, initial status) and the random slope over the 3 time periods will be calculated, and the time variable will represent the change in a particular outcome variable (ie, food security) over time within each participant. Level 2 (time nested within participant characteristics) will test whether treatment status (ie, control or experimental) and any nonequivalent baseline participant characteristics predict outcomes. If the ICC coefficient is greater than 0.10, a third level will be added to the model to control for clustering by center. Finally, participants will be clustered within centers (Level 3).

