## Results

The project was funded in October 2022. As indicated in the study progress (Figure 3), recruitment and screening started in June 2022. The research team recruited and screened 150 participants by the end of August 2022 at the 7 original target centers. Due to the low recruitment numbers, the number of centers and recruitment time were extended. Seven additional centers for recruitment were incorporated starting in September 2022. Power analysis was completed to ensure adequate recruitment numbers were met with the 14 centers. NIH was notified in writing of these changes. Fourteen centers were condensed to 12 centers (1 closed because of structural damage and 1 smaller center merged with a larger sister center).

A total of 578 older adults completed the screening, of whom 507 participants were eligible to participate in the study (88%). The 12 centers were randomly assigned into 2 study cohorts, which consisted of a total of 398 older adult participants. Cohort 1 consisted of 226 eligible participants, of whom 164 participants graduated from the program. Cohort 2 had 172 eligible participants, of whom 111 participants graduated from the program (Figure 4). Monthly bingo and informative presentations (nonnutrition and nonphysical activity–related) were conducted with Cohort 2 centers for engagement and retention. Focus groups were conducted for Cohort 1 postintervention in October 2023 and for Cohort 2 in June 2024 to assess the fidelity of the intervention. Data collection for Cohort 2 is currently ongoing. Preliminary data analysis is being conducted for all cohorts to evaluate the intervention’s outcomes.

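### Aim 3 includes the center level only if the ICC exceeds 0.10, although centers were randomized and the planning ICC is 0.016

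*Protocol article*

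**What the plan says.** Under Statistical Models, Aim 3, Level 1 is time (T0 to T3) with a random intercept and slope for each participant. Level 2 is the participant, and it "will test whether treatment status (ie, control or experimental) and any nonequivalent baseline participant characteristics predict outcomes". The center level is conditional: "If the ICC coefficient is greater than 0.10, a third level will be added to the model to control for clustering by center". The section then closes with "Finally, participants will be clustered within centers (Level 3".

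Three other places bear on this:

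- Design: "Each of the 12 centers was randomly assigned to one of 2 cohorts".
- Power Calculations and Estimation of Sample Size: the plan works "with an Interrelation Class Coefficient of 0.016" and says that this lowers the effective sample size.
- Statistical Models, Aims 1 and 2: both two-level models have center as Level 2, with no condition on the ICC.

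**The concern.** Treatment was allocated to 12 centers, so any comparison of cohorts carries between-center variation, whatever value the ICC happens to take. A model with only time and participant levels tests treatment as though participants had been randomized one by one. The article accepts that an ICC of 0.016 matters when it sizes the trial, then sets a bar 6.25 times higher (0.10 / 0.016) before the same clustering may enter the Aim 3 model. It gives no reason for treating Aim 3 differently from Aims 1 and 2.

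Twelve centers also give a poor estimate of an ICC, so the condition would let a noisy quantity choose the model, possibly a different one for each outcome. At stake are the standard errors for long-term effects on food security, diet quality and the other Aim 3 outcomes: too small where the contrast contains between-center variation, with effects then declared too often.

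**Working it through.** **Inputs.** Planning ICC 0.016, planned analytic N 410 and effective N 374 (Power Calculations); 12 centers (Design); 398 participants randomized (Abstract); 164 graduates of 226 in Cohort 1 and 111 of 172 in Cohort 2 (Results). Mean participants per center: 398/12 = 33.2, or (164 + 111)/12 = 275/12 = 22.9 for graduates. A two-sided 5% test and equal center sizes are assumed.

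**1. The plan's own figure.** With design effect DE = 1 + (m - 1) x ICC, the effective N of 374 reproduces at m = 7: DE = 1 + 6 x 0.016 = 1.096 and 410/1.096 = 374. So the plan does charge itself for an ICC of 0.016. (That m = 7 is far below the roughly 34 per center given by 410/12 is a separate matter.)

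**2. Would the condition ever be met?** Simulated data for 12 centers of 33 or 34 people, with the ICC estimated by analysis of variance (5,000 runs per value), gave these chances of an estimate above 0.10:

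| True center ICC | Chance that the center level is added |
|---|---|
| 0.016 | 0.06% |
| 0.05 | 6.6% |
| 0.10 | 43.6% |

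**3. Cohort comparison at one time point, center omitted.** The true standard error is sqrt(DE) times the reported one, so type I error = 2 x [1 - Phi(1.96/sqrt(DE))].

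| ICC | m = 33.2: DE, SE ratio, type I error | m = 22.9: DE, SE ratio, type I error |
|---|---|---|
| 0.016 | 1.51, 1.23, 11% | 1.35, 1.16, 9% |
| 0.05 | 2.61, 1.61, 22% | 2.10, 1.45, 18% |
| 0.099 | 4.18, 2.05, 34% | 3.17, 1.78, 27% |

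Simulation with 398 participants in 6 v 6 centers (4,000 runs) agrees: 11.1%, 23.2% and 35.2% at ICC 0.016, 0.05 and 0.0999.

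**4. Longitudinal contrasts, center omitted.** Aim 3 models change, so step 3 is only one case. The article does not give the correlations needed. Assumed: 33 per center, four equally spaced visits, total variance 1 at T0, within-person correlation 0.5, random-slope variance 0.02. With V the covariance the two-level model uses for one person and W the true covariance of all observations in a center, the reported variance is A^-1, where A = sum of X'V^-1X. The true variance is A^-1 B A^-1, where B = sum of X'V^-1 W V^-1X. With r the ratio of true to reported standard error, type I error = 2 x [1 - Phi(1.96/r)].

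| Coefficient tested | Center effect | ICC 0.016 | ICC 0.05 | ICC 0.099 |
|---|---|---|---|---|
| Cohort-by-time slope | stable over visits | 5% | 5% | 5% |
| Cohort-by-time slope | one fifth visit-specific | 7% | 11% | 17% |
| Time-varying treatment (Cohort 1 on from T1, Cohort 2 from T3) | stable over visits | 6% | 10% | 14% |
| Time-varying treatment | one fifth visit-specific | 8% | 15% | 23% |
| Cohort main effect over all visits | stable over visits | 14% | 29% | 42% |

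A stable center effect cancels from within-person change, which is why the first row shows no inflation. Variation of the center effect between visits does not cancel, and the two-level model omits that too.

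**The case against.** The strongest reply is that the closing Level 3 sentence carries no condition. If it governs, center is always in the model and no harm follows. That reading is possible, but the sentence comes directly after the rule and most naturally names the level the rule may add. If it is meant unconditionally, it contradicts the rule. Either way the text needs correcting.

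Second, the familiar design-effect figures describe a comparison at a single time point, whereas Aim 3 is a growth model. This stands: the article does not say which coefficient is tested, so no single inflation figure can be given, and for one plausible contrast there is none.

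Third, a reader might infer that the trial's primary analysis ignores clustering, or that a false-positive rate near one in three is to be expected. The documents support neither. Food security and diet quality are tested as primary outcomes under Aim 1, where center is always a level. The rates near one third need an ICC just below 0.10, about six times the planning value, and a contrast made wholly between centers.

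Fourth, robust standard errors are mentioned, but only under Aim 1, as one estimation option, and they are not said to be clustered by center. They do not rescue Aim 3.

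**Conclusion.** The rule is wrong as written and confined to Aim 3. At the planning ICC it would almost never admit the center level. Type I error at a nominal 5% would then be about 9-11% for a cohort comparison at one time point, 6-8% for a time-varying treatment effect, and 5-7% for a cohort-by-time slope. Just below the cut-off the corresponding ranges are 27-34%, 14-23% and 5-17%.

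The single-time-point ranges span 23 to 33 people per center. The other two span a stable center effect and one that is one fifth visit-specific, under the correlations assumed in step 4. All take the ICC in the rule to be the center ICC, which the article does not define but which fits the stated purpose of controlling for center, and all assume equal center sizes. Centers were stratified by size, and unequal sizes would usually raise the inflation. This should be fixed before the Aim 3 analysis; it does not threaten the primary test.

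**What to change.** - Delete the ICC > 0.10 condition and reconcile the closing sentence with the rest of the Aim 3 paragraph.
- Always fit three levels: visits within participants within centers. Keep the center random intercept whatever its estimated variance.
- Allow center-by-time variation, for example by a center-by-visit random effect. A center intercept alone does not protect a contrast in change over time.
- Use a small-sample correction for 12 centers, for example Kenward-Roger or Satterthwaite degrees of freedom.
- State which treatment coefficient answers Aim 3, and report the ICC descriptively.

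This costs a few sentences and no new data. The article reports 18-month data collection as ongoing, so the change can precede the final analysis. The downside is wider intervals. For a single-time-point comparison at ICC 0.016 with 33 per center, the standard error grows by 1.23. With 10 degrees of freedom the critical value rises from 1.96 to 2.23, so the interval is about 1.23 x 2.23/1.96 = 1.40 times as wide. For contrasts in within-person change the growth in standard error at that ICC is smaller.

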### Ethical Considerations

This study is approved by the University of Texas at San Antonio Institutional Review Board (IRB protocol FY20-21-241). The baseline phase of the study involved obtaining institutional review board approval through a comprehensive review, followed by participant recruitment and baseline data collection. During this phase, participants also reviewed and signed consent forms in writing.

Data are collected using Research Electronic Data Capture (REDCap; Vanderbilt University) surveys and are managed and stored in REDCap and in a UTSA-secured site where only the study team has access to participant files. REDCap is a secure, web-based software platform designed to support data capture for research studies, providing (1) an intuitive interface for validated data capture; (2) audit trails for tracking data manipulation and export procedures; (3) automated export procedures for seamless data downloads to common statistical packages; and (4) procedures for data integration and interoperability with external sources [70,71]. All data and records generated during this study comply with confidentiality procedures and protocols in accordance with UTSA and Health Insurance Portability and Accountability Act (HIPAA) policies. We will not share any identifiable data with outside study partners unless specified in the consent form. Data collection is the responsibility of the research study staff at the site under the supervision of the site investigator.

Participants receive a compensation of US $20 local grocery store gift card for each data collection event and the opportunity to win a US $5 local grocery store gift card during the bingo games.

## Results

The project was funded in October 2022. As indicated in the study progress (Figure 3), recruitment and screening started in June 2022. The research team recruited and screened 150 participants by the end of August 2022 at the 7 original target centers. Due to the low recruitment numbers, the number of centers and recruitment time were extended. Seven additional centers for recruitment were incorporated starting in September 2022. Power analysis was completed to ensure adequate recruitment numbers were met with the 14 centers. NIH was notified in writing of these changes. Fourteen centers were condensed to 12 centers (1 closed because of structural damage and 1 smaller center merged with a larger sister center).

A total of 578 older adults completed the screening, of whom 507 participants were eligible to participate in the study (88%). The 12 centers were randomly assigned into 2 study cohorts, which consisted of a total of 398 older adult participants. Cohort 1 consisted of 226 eligible participants, of whom 164 participants graduated from the program. Cohort 2 had 172 eligible participants, of whom 111 participants graduated from the program (Figure 4). Monthly bingo and informative presentations (nonnutrition and nonphysical activity–related) were conducted with Cohort 2 centers for engagement and retention. Focus groups were conducted for Cohort 1 postintervention in October 2023 and for Cohort 2 in June 2024 to assess the fidelity of the intervention. Data collection for Cohort 2 is currently ongoing. Preliminary data analysis is being conducted for all cohorts to evaluate the intervention’s outcomes.

**Figure 3. F3:**
[figure not shown]
Study progress.

**Figure 4. F4:**
[figure not shown]
Consolidated Standards of Reporting Trials (CONSORT) flow diagram.

## Discussion

### Principal Considerations

Inadequate nutrition and a lack of physical activity can lead to complications from chronic diseases in older adults and a decline in health [72,73]. The COVID-19 pandemic disrupted essential nutrition services like CMP sites in San Antonio, Texas [18]. The “digital divide” exacerbated the negative impact of the COVID-19 pandemic on older adults [18]. To address this, improving technology access and knowledge, and providing evidence-based online nutrition programs are essential and have the potential to benefit the vulnerable homebound population, thereby becoming an integral part of OAA-funded services.   

### Strengths and Limitations

The program’s strengths lie in the potential for its integration into the existing CMP infrastructure, bolstering support and resources for participants most in need. The proposed intervention follows a community-based participatory research approach, seeking essential input and feedback from the DHS Senior Services, OATS, and older adult CMP participants to enhance the intervention’s chances of success [74]. Seeking the assistance of the voluntary peer navigators at the centers provided additional in-person support to participants experiencing challenges in completing the intervention. The technology intervention addresses key barriers to older adults adopting technology by providing internet services and devices, offering support through a 5-week training program conducted by OATS, and providing continued technical support and internet access for one year [14,41]. In addition, OATS also provided practice Zoom sessions and in-person help to improve participant self-efficacy in navigating through the Zoom sessions and the nutrition modules in Google Classroom. The DHS team acted as a medium of communication between the study team and the participants.

A second strength of the study is the closed-cohort stepped-wedge design. In this approach, cohorts are randomly assigned the timing of the intervention, with a sequential transition from control to intervention for each cohort until all participants have received the intervention. This design ensures that all participants benefit from the intervention and allows each group to serve as its own control. It is practical when resources are limited and allows for the analysis of the influence of time on the intervention’s effectiveness.

Given the increased reliance on technology post-COVID-19, offering a digital nutrition intervention has the potential to positively impact food security and diet quality among vulnerable populations [75]. Moreover, this project has the potential to enhance physical activity, improve socialization, and mitigate loneliness in an at-risk, predominantly Hispanic population in South Texas.

Although the proposed intervention offers technology training, support, and access to the internet and devices, some limitations exist. A few participants may continue to experience challenges in understanding and using technology to engage in the online nutrition sessions conducted via Zoom. Moreover, the technical support and internet access provided by OATS ceased after the one-year service period, thereby restricting participants from using their devices except at the CMP site or locations offering complimentary Wi-Fi connectivity. Furthermore, the accuracy of survey completion may be affected by recall bias and introspective ability. To enhance the long-term sustainability of the project, mitigate associated costs, and strengthen the scope of incorporation into OAA services, it is important to investigate alternative options that offer low-cost internet access and affordable devices.

### Conclusions

This intervention study, conducted in collaboration with community partners and older adults, is focused on delivering a culturally tailored digital nutrition curriculum to at-risk older adults who frequently attend congregate meal sites. This initiative followed the allocation of technological resources and requisite support. The study’s developed materials are designed for implementation across all senior center locations in San Antonio. If successful, the project has the potential to reach over 2000 older adult congregate meal participants throughout San Antonio. Furthermore, it could serve as a replicable model for other OAA-funded nutrition services. The study’s outcomes will be disseminated through publication in high-impact journals and presentations at regional and national nutrition conferences dedicated to nutrition and aging.
